## Abstract

**Background:**

Adequate and intensive rehabilitation is an important requirement for successful Total Knee Arthroplasty. The primary focus of early rehabilitation is ambulation of patients and regaining range of motion in the knee.

Although research suggests that Continuous Passive Motion should be implemented in the first rehabilitation phase following surgery, there is substantial debate about the duration of each session and the total period of CPM application and. A Cochrane review on this topic concluded that short-term use of CPM leads to greater short-term range of motion. It also suggested, however, that future research should concentrate on the treatment period during which CPM should be administered.

**Methods:**

In a randomised controlled trial we intend to investigate the efficacy of prolonged use of a continuous passive motion (CPM) device in the home situation as an adjunct to standardised physical therapy. The experimental treatment is compared to standardised physical therapy, in patients with osteoarthritis of the knee undergoing Total Knee Arthroplasty (TKA). Efficacy will be assessed in terms of faster improvements in range of motion and functional recovery.

Seventy patients with knee osteoarthritis undergoing TKA and experiencing early postoperative flexion impairment (less than 80° of knee flexion at the time of discharge) will be randomised over two treatment groups, a usual care group and an experimental group

The experimental group will receive CPM + physiotherapy for 17 consecutive days after surgery, whereas the usual care group will receive the same treatment during the in-hospital phase (i.e. about four days), followed by physical therapy alone (usual care) in the first two weeks after hospital discharge.

From 18 days to three months after discharge, both groups will receive standardised PT. The primary focus of rehabilitation will be functional recovery (e.g. ambulation) and regaining range of motion (ROM) in the knee.

**Discussion:**

Because restricted knee ROM affects functional activities, knee ROM and knee function are regarded as the primary indicators of successful TKA. Potential effects of the intervention under study include rapid return of knee flexion accompanied by earlier return to functional activities of daily life. If patients benefit significantly from prolonged CPM use, this treatment should be added to the standard PT treatment at home.

We expect the additional home CPM programme to be more effective than the usual physiotherapy programme, resulting in a difference in ROM of at least 5°, 17 days after surgery. This clinically important difference, with a possible flexion ROM of about 100°, is expected to lead to better functioning in activities of daily life, like walking, and earlier ability to cycle. These advantages should result in earlier and increasing independence.

## Background

With the ageing of the population, the prevalence of degenerative joint diseases is increasing. Reports show that over a one-year period, 25% of people over 55 years have a persistent episode of knee pain, of whom annually about one in six consult their general practitioner, in both the UK and the Netherlands. The prevalence of painful disabling knee osteoarthritis in people over 55 years is 10%, of whom one quarter are severely disabled. In all, over 300,000 Dutch residents currently suffer from knee osteoartritis (OA). Total Knee Arthroplasty (TKA) is a common intervention that can enhance the quality of life for patients with knee OA. Over 7500 TKAs are performed in Dutch hospitals every year. In 2003, 160 TKAs were performed at the Maastricht University Hospital.

Adequate and intensive rehabilitation is an important requirement for successful TKA. The primary focus of early rehabilitation is ambulation and regaining range of motion (ROM) in the knee. Because restricted knee ROM affects functional activities, knee ROM is regarded as one of the primary indicators of a successful TKA. Rapid return of knee flexion accompanied by earlier return to functional activities of daily life is one of the potential effects of the intervention we are proposing to study.

Although research findings favour the use of Continuous Passive Motion (CPM) in the first rehabilitation phase following surgery [1-4], there is substantial debate about the total period of CPM application and the duration of individual sessions. A Cochrane review [1] on the topic concluded that short-term use of CPM leads to a more rapid recovery of rabnge of motion. It also suggested, however, that future research should concentrate on the period during which CPM should be administered, and therefore called for research into longer-term use, involving long-term follow-up.

Before the year 2000, discharge from the Maastricht University Hospital after TKA was scheduled approximately 14 days after surgery. Nowadays, most patients are discharged four days after surgery. Since the time spent in hospital following surgery has decreased, continuation of CPM after hospital discharge might be beneficial. Although CPM is increasingly being administered in the postclinical home situation in recent years and is beginning to become part of the usual care programme, proper research into the effectiveness of a prolonged use of CPM at home is still lacking [1,2]. The only study that has been reported [5] compared CPM with physical therapy (PT) as a stand-alone therapy, whereas in the study presented here, CPM will be added to a standardised programme, adequately reflecting current practice.

This study is expected to provide new insights into the additional effects of CPM and to provide evidence to justify or refute its use.

Currently, orthopaedic surgeons at the hospital and physiotherapists at the hospital and at home play an important role in the rehabilitation process for TKA patients. The proposal presented here involves the same health care professionals and the same treatment strategies currently in use, but one patient group will additionally receive CPM at home.

We expect the effect of CPM treatment to be a quicker restoration of ROM, resulting in improved ADL function during the first 3 months after surgery.

Knee flexion values of 95° and 105° are regarded as range of motion benchmarks [6] in the functional recovery following CPM. While 95° of knee flexion allows normal ADL function, 105° of flexion gives a person the opportunity to ride a bicycle. This is of great advantage both in daily life (at least in the Netherlands) and in the rehabilitation from TKA surgery, because cycling allows patients to move the knee much more. We expect that prolonged use of CPM at home will allow patients to achieve these ROM benchmarks earlier in their recovery process.

About 50% of the patients undergoing one of the 160 TKAs performed annually at the Maastricht University Hospital have less than 80° of flexion 4 days after surgery and therefore potentially meet the inclusion criteria of the proposed study.

If the study should find that patients benefit from home CPM, this treatment should be added to the standard PT treatment currently administered. No differences in direct costs of rehabilitation are expected from implementation of the study results.

### Objective

Continuous passive motion (CPM) has proved to increase the amount of knee flexion for knee patients in the acute hospital setting (5–10 days). The primary purpose of the proposed randomised controlled trial is to establish whether there is additional long term benefit of continuing CPM after hospital discharge.

### Research question

What is the effect on range of motion and functional status of prolonged use of a continuous passive motion device at home in addition to physical therapy, compared to physical therapy alone, in patients with limited flexion range of motion (less than 80°) of the knee at discharge from the hospital following total knee arthroplasty?

## Methods/Design

### Study design

The proposed study is a randomised controlled trial, with blinded treatment allocation, assessment and analysis, in which 70 patients undergoing a scheduled unilateral TKA will be evaluated to assess the added value of CPM at home, using function and mobility as the main outcomes.

### Participants

We intend to include 70 patients in the study, who must be eligible for unilateral primary TKA as a result of osteoarthritis of the knee. Patients will be included if they have less than 80° of flexion range of motion 4 days after surgery, are able to understand and speak Dutch, are not suffering from mental disabilities and are resident inside the 'Maastricht heuvelland' region. Patients will be excluded if they need to stay in hospital for more than 5 days after surgery or show relevant co-morbidity influencing mobility (e.g. claudication, other prosthesis) or are operated upon using minimally invasive surgery.

Eligible patients will be contacted one week before planned surgery, and will be randomised into two groups after signing an informed consent form, on the day they are discharged from hospital. Patients will thus have 10 days in which to consider participation.

Blocked and concealed randomisation with a block size of 4 will ensure equal distribution of patients over the two treatment groups. Groups will be prestratified on preoperative flexion mobility of the knee.

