### Interventions

During the in-hospital period, all patients will receive a standardised PT programme, involving 20 minutes of PT per day for four days. During the first two weeks after discharge, patients in the experimental group will receive CPM for 4 hours a day in addition to regular PT treatment. Patients in the control group will receive only regular PT treatment (usual care).

From day 18 onward, all patients will receive regular PT treatment until 3 months after surgery, if indicated.

The post-clinical PT will be standardised in terms of treatment objectives. All patients will receive treatment consisting of active and passive mobilisation of the knee joint, active strengthening of the m. quadriceps, and training of ADL functions (gait, sit to stand and stair climbing).

Outcome assessment

After baseline variables have been collected, outcome measures will be assessed at 17 days, 6 weeks and 3 months after surgery, during normal routine assessments at the orthopaedic clinic (table 1). The outcome assessor will be blinded.

Primary outcome measures are:

1. functional status, using the WOMAC function score [7,8] and the Knee Society Score[9]; and

2. range of motion, assessed with a long-arm goniometer [10].

Secondary outcome measures are:

a. perceived effect, using a 7-point Likert scale;

b. postoperative medication use (amount; type will be standardised);

c. satisfaction with treatment, on an 11-point Likert scale;

d. satisfaction with treatment result, on an 11-point Likert scale;

e. adherence to treatment protocols and use of CPM (in hours), measured with a patient diary;

f. quantity, duration and nature of PT intervention.

The study design is depicted in figure 1

The first primary endpoint of the study is on day 17 after surgery, which is when the experimental treatment stops and short-term effects are measured.

The second endpoint is at 3 months after surgery.

Table 1 shows the timing of the outcome assessment

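### A single fixed block size of 4 could let recruiting staff who track allocations by stratum foresee up to about 30–32% of assignments; varying, undisclosed block sizes are a minor, cheap improvement

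*Protocol article*

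**What the plan says.** The Participants section of the protocol article fixes the randomisation in two sentences. The first gives a single block size: "Blocked and concealed randomisation with a block size of 4 will ensure equal distribution of patients over the two treatment groups". The second adds stratification: "Groups will be prestratified on preoperative flexion mobility of the knee". Neither the number of strata nor the cut-off is given. The target is stated as "We intend to include 70 patients in the study". Patients are randomised "after signing an informed consent form, on the day they are discharged from hospital". The Study design section describes treatment allocation, assessment and analysis as blinded.

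On visibility, the Interventions section says that for the first two weeks after discharge "patients in the experimental group will receive CPM for 4 hours a day in addition to regular PT treatment", while controls have regular physiotherapy only. No sham device is described. The blinding spelled out later covers the outcome assessor and the analyst.

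On setting, the Background section refers to "About 50% of the patients undergoing one of the 160 TKAs performed annually at the Maastricht University Hospital", and the Participants section limits entry to one region. A single recruiting hospital is a fair inference, though the article does not use that term.

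**The concern.** Concealment has two parts: the list must be hidden, and the next entry must not be deducible from the entries already used. A constant block of 4 is weak on the second part when earlier assignments can be learned. In every block the fourth assignment follows from the first three, and sometimes the third follows from the first two.

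If the person who settles eligibility or final consent can foresee the arm, enrolment can be tilted, even unintentionally. Three decisions fall close enough to randomisation for this to matter: the flexion reading on day 4 against the 80° limit, the criterion on stay beyond 5 days, and final consent around discharge. Flexion is also the variable on which the trial is powered. Analysis by intention to treat and a blinded assessor protect what happens after randomisation. They do not correct for who was enrolled.

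**Working it through.** The plan gives no predictability figure, so there is none to reproduce.

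**Inputs**
- From Participants: block size 4, two equal arms (2 and 2 per block), 70 patients, stratified by preoperative flexion.
- Assumed: 1 to 4 strata of near-equal size, because the number is not stated.
- Assumed: an observer who knows the block size, where each block starts, and every earlier allocation in the same stratum.

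**Certain allocations per block.** There are 6 equally likely orders. In AABB and BBAA the last two assignments are determined. In the other four orders only the last is.
- Expected number: (2×2 + 4×1)/6 = 4/3 per block, or 1/3 of allocations.
- By position, the probability of certainty is 0, 0, 1/3 and 1.

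**Applied to 70 patients, with incomplete last blocks**
- One list: 17 full blocks and 2 patients over: 17 × 4/3 + 0 = 22.7, or 32.4%.
- Two strata of 35: each has 8 full blocks and 3 patients over: 2 × (8 × 4/3 + 1/3) = 22.0, or 31.4%. A 34/36 split gives 22.7, or 32.4%.
- Three strata (23, 23, 24): 7 + 7 + 8 = 22.0, or 31.4%.
- Four strata (17, 17, 18, 18): 4 × (4 × 4/3) = 21.3, or 30.5%.

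The ceiling is therefore 21.3 to 22.7 patients, about 30–32%.

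**Best guess.** The observer always names the arm with more places left.
- Success by position is 1/2, 2/3, 2/3 and 1. The sum is 17/6, so 17/24 = 70.8% in full blocks, against 50% by chance.
- For 70 patients in one list: 17 × 17/6 + 1/2 + 2/3 = 49.3, or 70.5%.

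**Observer who does not track stratum** (two strata, simulation). A guess from the overall running balance is right about 65% of the time, and the counts of certain allocations above no longer apply.

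**Effect of varying the block size** (simulation, one list of 70; the observer knows the set of sizes but not the size of any given block)

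| Block sizes | Certain | Best guess right |
|---|---|---|
| 4 fixed | about 32% | about 71% |
| 4 and 6 | about 5–6% | about 69% |
| 4, 6 and 8 | about 2% | about 68% |

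Sizes 4 and 6 therefore leave about 4 certain allocations (5.5% of 70 = 3.8) instead of about 22. The advantage from guessing hardly changes.

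**The case against.** The strongest reply is that the arithmetic describes an observer whom the article does not describe. A reader might infer that a third of allocations are in fact predictable and that the stated concealment is undermined. The documents do not support that. The list can stay concealed with a fixed block of 4. Prediction also needs the block starts and all earlier allocations, stratum by stratum, and stratification means that several block sequences may run at once. This part of the reply stands, so the figure is a ceiling. It does not remove the point: preoperative flexion is known before randomisation, so tracking by stratum is harder but possible.

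A reader might also infer that recruiting staff see who goes home with a device. The article says only that one arm receives home CPM. It does not say who supplies the device, who enrols patients, or whether recruiters learn earlier allocations.

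The co-morbidity exclusion (patients who "show relevant co-morbidity influencing mobility (e.g. claudication, other prosthesis") might look like a judgement open to influence at randomisation. Yet eligible patients are contacted a week before surgery, and the examples given can be known by then. The Background figures allow at most about 80 candidates a year (50% of 160), or about 1.5 a week. Other allocations can therefore fall between that screening and the patient's own randomisation. The opening is narrower than the full eligibility list, but the decisions close to discharge remain.

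Finally, it is tempting to ask who generates and holds the list and when an allocation is released. The article already states concealed randomisation after signed consent, and a condensed article may leave the rest to the full protocol. That is not a finding.

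**Conclusion.** The point holds as a minor design weakness. A single block size of 4 within strata, in a trial that appears to have one hospital and has visibly different arms, leaves up to about 30–32% of 70 allocations (about 21 to 23 patients) open to certain prediction. This rests on two assumptions: that recruiting staff know the block size, which the article prints, and that they learn earlier allocations by stratum, on which the article is silent. The documents do not contradict themselves here, and nothing in them shows that concealment fails. The size of any resulting bias in flexion or function cannot be derived from them. The argument for change is that a known route to selective enrolment can be largely closed, as far as certain allocations go, at almost no cost.

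**What to change.** Replace the fixed block of 4 with randomly varying block sizes, for example 4 and 6, within each preoperative-flexion stratum. Do not disclose the sizes to recruiting staff.

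The gain is in certainty, where known allocations fall from about 30–32% to about 5–6%. It should not be presented as making allocation hard to guess, because the best-guess rate falls only from about 70–71% to 69%.

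The cost is a regenerated list and slightly looser balance: the largest possible imbalance within a stratum rises from 2 (half of 4) to 3 (half of 6). Sample size, visits and analysis are unchanged.

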### Interventions

During the in-hospital period, all patients will receive a standardised PT programme, involving 20 minutes of PT per day for four days. During the first two weeks after discharge, patients in the experimental group will receive CPM for 4 hours a day in addition to regular PT treatment. Patients in the control group will receive only regular PT treatment (usual care).

From day 18 onward, all patients will receive regular PT treatment until 3 months after surgery, if indicated.

The post-clinical PT will be standardised in terms of treatment objectives. All patients will receive treatment consisting of active and passive mobilisation of the knee joint, active strengthening of the m. quadriceps, and training of ADL functions (gait, sit to stand and stair climbing).

Outcome assessment

After baseline variables have been collected, outcome measures will be assessed at 17 days, 6 weeks and 3 months after surgery, during normal routine assessments at the orthopaedic clinic (table 1). The outcome assessor will be blinded.

Primary outcome measures are:

1. functional status, using the WOMAC function score [7,8] and the Knee Society Score[9]; and

2. range of motion, assessed with a long-arm goniometer [10].

Secondary outcome measures are:

a. perceived effect, using a 7-point Likert scale;

b. postoperative medication use (amount; type will be standardised);

c. satisfaction with treatment, on an 11-point Likert scale;

d. satisfaction with treatment result, on an 11-point Likert scale;

e. adherence to treatment protocols and use of CPM (in hours), measured with a patient diary;

f. quantity, duration and nature of PT intervention.

The study design is depicted in figure 1

The first primary endpoint of the study is on day 17 after surgery, which is when the experimental treatment stops and short-term effects are measured.

The second endpoint is at 3 months after surgery.

Table 1 shows the timing of the outcome assessment

### Power analyses

We assume a difference of more than 5° of knee flexion mobility (SD 8°) at the end of the CPM application to be clinically relevant. With an alpha of 0.05, and a power of 80%, we will need 28 patients per group to prove this.

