### Data analysis

Data will be stored and analysed with SPSS-12.0 After checks for missing values and for normality of the data, regression techniques will be applied by a blinded analyst using the 'intention-to-treat' principle. Primary and secondary outcome measures will be reported for the in-hospital and home situations, and for 6-week and 3-month follow-up.

The primary research question will be tested using Student's t-tests with a p-value of 0.05 being regarded as significant.

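### The 28 patients per group do not follow from the stated inputs: two-sided power for 5° (SD 8°) is about 63%, not 80%, and about 73% with all 70 patients

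*Protocol article*

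**What the plan says.** The Power analyses section sets the design difference and its spread: "We assume a difference of more than 5° of knee flexion mobility (SD 8°) at the end of the CPM application to be clinically relevant". It then gives the result: "With an alpha of 0.05, and a power of 80%, we will need 28 patients per group to prove this". Whether alpha is one- or two-sided is not said.

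The Discussion part of the abstract names the same threshold, expecting home CPM to do better, "resulting in a difference in ROM of at least 5°, 17 days after surgery", and calls this difference clinically important.

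Under Participants the planned total is larger than 2 × 28 = 56: "We intend to include 70 patients in the study". Blocked randomisation into equal groups makes that 35 per group. The article does not explain the additional 14 patients.

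The Data analysis section fixes the test: "The primary research question will be tested using Student's t-tests", at a 0.05 significance level. It also mentions regression techniques, without tying them to the primary question.

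**The concern.** A standardised difference of 5/8 = 0.625 at 80% power and two-sided 0.05 calls for about 40 patients per group, so 28 looks too small at once. It is the only sample-size justification in the article.

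The consequence lies in how a null result would be read. The Background says the trial should help to justify or refute the use of home CPM, and the Dissemination section plans to carry the findings into guidelines and to insurers. If readers believe that a true 5° effect had only a 20% chance of being missed when that chance was substantially higher, a non-significant result will count for more against home CPM than it should.

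**Working it through.** **Inputs.** Difference 5°, SD 8°, alpha 0.05, power 80%, stated n = 28 per group (Power analyses); equal allocation and 70 patients, so 35 per group (Participants); two-sample Student's t-test (Data analysis). Sidedness is not stated, so both are computed.

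**Attempt to reproduce 28 (normal approximation).** n per group = 2 × (z for alpha + z for power)² × SD² / difference².

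- Two-sided: 2 × (1.960 + 0.8416)² × 64/25 = 40.2, so 41.
- One-sided: 2 × (1.645 + 0.8416)² × 64/25 = 31.7, so 32.
- One-sample or paired formula, two-sided (no factor 2): 20.1, so 21.

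None of these gives 28.

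**Exact power for the t-test.** Noncentral t with 2n − 2 degrees of freedom and noncentrality 5 / (8 × √(2/n)). For n = 28 the noncentrality is 2.339 with 54 degrees of freedom; for n = 35 it is 2.615 with 68.

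| n per group | Power, two-sided 0.05 | Power, one-sided 0.05 |
|---|---|---|
| 28 | 63.2% | 74.7% |
| 33 | 70.6% | 80.7% |
| 35 | 73.2% | 82.7% |
| 41 | 79.8% | 87.7% |
| 42 | 80.8% | 88.4% |

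The smallest n reaching 80% is 42 per group two-sided (84 evaluable patients) and 33 per group one-sided (66 evaluable).

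**Difference detectable at 80% power** (two-sided t-test, SD 8°): 6.1° with 28 per group, 5.4° with 35 per group.

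**Inputs that would give 28 per group** (two-sided 0.05, 80% power):

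- SD of about 6.6° with a 5° difference (exact t-test; 6.7° by the normal approximation).
- Difference of 6.1° with SD 8° (exact t-test). By the normal approximation a difference of 6° suffices: 2 × 2.8016² × 64/36 = 27.9, so 28. The exact t-test needs 29 for 6°, and 28 gives 78.7%.
- Adjustment for a baseline value correlated at about 0.57 with the outcome (0.55 by the normal approximation).

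None of these values is printed in the article.

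**The extra 14 patients.** 56 / (1 − 0.20) = 70, so they would fit a 20% dropout allowance. The article does not say so; this is an assumption. If it is right, the analysed sample returns to 28 per group and 63.2% two-sided power.

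**The case against.** Four points can be made for the plan.

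1. *Sidedness is open.* At one-sided 0.05, all 70 patients give 82.7%, above the target. This is correct, and it makes the 73% figure conditional on a two-sided test. But two-sided is the usual reading of an unqualified alpha of 0.05, nothing in the article announces a one-sided test, and one-sided testing still needs 33 per group rather than 28.

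2. *The design difference is worded as exceeding 5°, and 6° reproduces 28 by the normal approximation.* This may be where the figure came from, and on that reading 35 per group would have 87% power for 6°. The article therefore does not settle whether the fault is a slip in calculation or an unstated input. However, 6° appears nowhere and the abstract puts the clinically important threshold at 5° or more. A reader given 5° and SD 8° is told something untrue about the power.

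3. *Baseline adjustment could supply the missing power.* Randomisation is stratified on preoperative flexion and regression is mentioned. A correlation of about 0.39 would give 80% with 35 per group and no loss. But no correlation is stated, and the primary question is assigned to t-tests.

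4. *At the planned enrolment the shortfall is modest.* It is 73% against 80%, or 5.4° against 5°. That holds if nobody is lost. The 37% miss rate applies only if 56 patients are analysed, and the 20% dropout behind that number is inferred.

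These points narrow the size and the conditions of the shortfall. None of them makes 28 per group correct for the inputs given.

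**Conclusion.** The concern holds. The sample size of 28 per group cannot be derived from a 5° difference, SD 8°, alpha 0.05 and 80% power under either sidedness; it falls one third short of the 42 needed two-sided (28/42 = 0.67).

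For the stated t-test, taken as two-sided and unadjusted, the probability of missing a true 5° effect is 27% with all 70 patients analysed and 37% with 56, against the 20% claimed. The first figure assumes no dropout; the second corresponds to the stated 28 per group. The conclusion about the 70 patients depends on two-sided testing; the conclusion about the 28 does not.

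**What to change.** Rewrite the Power analyses paragraph so that inputs and result agree:

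- State that the test is two-sided and that the design difference is 5° with SD 8°. If a different difference or SD was used, print it and justify it.
- Report the power the trial has with an unadjusted t-test: 73% with 70 patients analysed, 63% with 56. Equivalently, 80% power corresponds to 5.4° with 35 per group or 6.1° with 28.
- Say what the 14 patients beyond 56 are for and, if they allow for dropout, give the assumed rate.

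If the sponsor wants to keep 80% power for 5° with 70 patients, the primary test should become a baseline-adjusted comparison, with the assumed correlation stated and supported. About 0.39 is needed with 35 analysed per group, and about 0.57 if only 28 per group are analysed. The Data analysis section would have to name that model in place of the t-test. Keeping the unadjusted two-sided t-test at 80% would instead require 84 evaluable patients, 14 more than planned before any loss.

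The restatement costs one paragraph and a less favourable power figure; it needs no additional patients. The adjusted analysis uses the preoperative flexion already needed for stratification and requires a change to the analysis text.
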